### Outcomes

#### Primary endpoint

Sensitivity and specificity for a multi-parametric diagnostic model, incorporating different pathogen- and host-related factors, in differentiating between bacterial and viral aetiology in patients with LRTI and/or sepsis.

#### Secondary endpoints

Sensitivity and specificity for host-related individual blood biomarkers, in differentiating between bacterial and viral aetiology from other aetiologist in patients with LRTI and/or sepsis;Sensitivity and specificity for host-related sets of blood biomarkers, in differentiating Gram positive or Gram negative or atypical aetiology from other disease aetiologist in patients with LRTI and/or sepsis;Monitoring the temporal dynamics of host-related blood biomarkers levels during the course of disease in patients with LRTI and/or sepsis;A list of significant bacterial microbiome components that are associated with poor or favourable clinical outcome in patients with LRTI and/or sepsis;Sensitivity and specificity for liquid chromatography-mass spectrometry (LC-MS/MS) and lipid-based Protein Immobilization (LPI) proteomics-based rapid detection technique in identifying pathogens in clinical samples of patients with LRTI and/or sepsis;A web-based application that recommends physicians with a preferred antimicrobial treatment based on patients clinical, molecular and biochemical data;To define genetic mechanisms underlying the different host response between patients with viral versus bacterial infection.

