#### Secondary objectives

Identify individual as well as sets of blood host biomarkers for differentiating between bacterial, and viral aetiologies and determine the sensitivity and specificity of these biomarkers in distinguishing between the different infection types;Identify individual as well as sets of blood host biomarkers for differentiating between bacterial subtypes, namely Gram positive, Gram negative and atypical bacteria;Characterize the temporal dynamics of the host-pathogen interactions based on multiple sampling before and during antimicrobial treatment;Characterize the respiratory microbiome in patients presenting with LRTI and/or sepsis;Develop a mass spectrometry based, rapid detection technique for identification of microbial pathogens and antimicrobial resistances in clinical samples;Develop a personalized treatment algorithm for tailored antimicrobial therapy that integrates clinical, molecular and biochemical data;Define genetic mechanisms underlying the differential host response between patients with viral versus bacterial infection.

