#### Paediatric population analysis

First, we estimate the sample size required to reject the null hypothesis that the sensitivity over the entire population, P, is lower than P0 = 70% (H0: P ≤ P0, H1: P > P0) with significance level of 1% (α = 0.01), power of 80% (=1-β) for a true sensitivity P1 of 90% (P1 - P0 ≥ 0.2). For sufficiently large sample sizes (n > ~ 30) the sample distribution of the sensitivity, is approximately normally distributed, ($$ \widehat{p} $$ ~ N{P, P(1-P)/n}). Thus, the number of bacterial patients that are required is:$$ \mathrm{n}=\frac{{\left({\mathrm{Z}}_{1-\upalpha}\sqrt{{\mathrm{P}}_0\left(1-{\mathrm{P}}_0\right)}+{\mathrm{Z}}_{1-\upbeta}\sqrt{{\mathrm{P}}_1\left(1-{\mathrm{P}}_1\right)}\right)}^2}{{\left({\mathrm{P}}_1-{\mathrm{P}}_0\right)}^2}\le 76 $$

We estimate that the ratio between bacterial and viral paediatric patients is 1:3 and that expert consensus is achieved in 65% of the cases. Thus, the number of patients with an acute infection required in order to reach 76 bacterial patients is 468 = (76 / 25% / 65%). Using similar considerations for computing specificity the sample size for viral patients is also 76. Of note, we anticipate that the above mentioned 468 patients will include 229 (= 468 × 75% × 65%) viral patients, and thus there is no need for additional patients. To assess the host-response based diagnostics accuracy in differentiating patients with an acute infection (both viral and bacterial) and non-infectious patients, assuming P0 = 70% (H0: P ≤ P0, H1: P > P0) with significance level of 1% (α = 0.01), power of 80% (=1-β) for a true sensitivity P1 of 90% (P1 - P0 ≥ 0.2) requires 76 non-infectious patients. Overall, the paediatric cohort should include at least 468 patients with a suspected infectious disease and 76 patients with non-infectious.

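### The Gram-subtype endpoint compares each bacterial subtype with other disease aetiologies, while its objective is to tell bacterial subtypes apart, so its specificity in children mostly reflects bacterial-versus-viral separation

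*Protocol article*

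**What the plan says.** Under Secondary objectives, the protocol article sets out to identify "blood host biomarkers for differentiating between bacterial subtypes, namely Gram positive, Gram negative and atypical bacteria". This is a contrast among patients who all have a bacterial infection.

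Under Secondary endpoints, the matching item is the sensitivity and specificity of sets of blood biomarkers "in differentiating Gram positive or Gram negative or atypical aetiology from other disease aetiologist in patients with LRTI and/or sepsis" (the noun is evidently a misprint for aetiologies). No other endpoint deals with Gram type, and no section limits this one to bacterial patients or adds a comparison within them.

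The case mix is given under Paediatric population analysis: "We estimate that the ratio between bacterial and viral paediatric patients is 1:3 and that expert consensus is achieved in 65% of the cases". The same paragraph works with 76 bacterial children and says that the "468 patients will include 229 (= 468 × 75% × 65%) viral patients". It adds 76 non-infectious children. Adult population analysis assumes a viral-to-bacterial rate of 3:7 among 390 infectious adults, the same consensus rate, and 76 non-infectious adults.

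**The concern.** The objective and its endpoint name different comparators. A viral infection is another disease aetiology in a patient with LRTI or sepsis, so viral patients enter the specificity denominator of each subtype. In children they outnumber bacterial patients three to one. The reported specificity would then mainly show how well the set separates bacterial from viral disease, which the primary endpoint and the first secondary endpoint already cover.

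A set that recognises bacterial infection but cannot tell one subtype from another could therefore show high sensitivity and fairly high specificity for Gram-positive disease in children. That could be read as evidence that host markers separate the subtypes. The distinction matters to the article's own rationale: the section on the burden of antibiotic misuse names the wrong antibiotic spectrum as the third type of misuse, and the contrast within bacterial patients is the one that bears on it. The problem does not depend on how the subtype label is obtained. It remains with a perfect pathogen label.

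**Working it through.** **Plan figures reproduced**

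- Children: 76 / 0.25 / 0.65 = 467.7, stated as 468.
- Children with consensus: bacterial 468 × 0.25 × 0.65 = 76.05; viral 468 × 0.75 × 0.65 = 228.15 (printed as 229, an immaterial rounding difference). I use 76 and 228.
- Adults with consensus: bacterial 390 × 0.70 × 0.65 = 177.45; viral 390 × 0.30 × 0.65 = 76.05. I use 177 and 76.
- Non-infectious: 76 in each age group.

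**Assumptions that are not in the article**

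- The marker set is positive in 90% of bacterial patients, whatever the subtype, and in 10% of all other patients. It carries no subtype information.
- The target subtype makes up a share f of the bacterial patients, varied from 30% to 70%, with 10% for a rarer subtype.
- Every bacterial patient has a subtype label.

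**Formula**

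Let B be the number of bacterial patients and N the number of non-bacterial comparators. Sensitivity for the target subtype is 90%. Specificity against other aetiologies is

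[0.10 × B(1 − f) + 0.90 × N] / [B(1 − f) + N].

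Against other bacterial patients only, N = 0 and specificity is 10% for every f.

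**Worked example: children, f = 50%**

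Other bacterial patients: 76 × 0.5 = 38.

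- Viral comparators only: (3.8 + 205.2) / (38 + 228) = 209.0 / 266 = 78.6%.
- With 76 non-infectious added, N = 304: (3.8 + 273.6) / (38 + 304) = 277.4 / 342 = 81.1%.

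Viral patients make up 228 / 266 = 86% of the first denominator.

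**Results for a set with no subtype information**

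| Group, comparators | f = 30% | f = 50% | f = 70% |
|---|---|---|---|
| Children, viral + other bacterial | 74.9% | 78.6% | 82.7% |
| Children, non-infectious also counted | 78.1% | 81.1% | 84.4% |
| Adults, viral + other bacterial | 40.4% | 47.0% | 57.1% |
| Adults, non-infectious also counted | 54.1% | 60.6% | 69.3% |
| Either group, other bacterial only | 10% | 10% | 10% |

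**Rarer subtype: children, f = 10%**

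Other bacterial patients: 76 × 0.9 = 68.4.

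- Viral comparators only: (6.84 + 205.2) / 296.4 = 71.5%.
- With non-infectious: (6.84 + 273.6) / 372.4 = 75.3%.

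**Sensitivity to marker quality**

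If the set is negative in only 80% of non-bacterial patients, the paediatric figures at f = one third are about 67% (viral comparators only) and 70% (with non-infectious). The 90%/90% set gives about 76% and 79% at the same share.

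**The case against.** **One-versus-rest is a legitimate measure.** Patients present undifferentiated, so asking whether a Gram-negative case can be told from everything else is a real diagnostic question. The comparator includes the other bacterial subtypes, so the endpoint overlaps the objective. Reading the three subtype results together could also expose a set that flags the same patients each time. This supports keeping the comparison as a supplementary result. It does not make it an answer to an objective framed as a contrast between bacterial subtypes.

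**The article condenses a fuller document.** Comparator sets are often detailed elsewhere, and the clause is visibly garbled. But the article does state a comparator, and it differs from that of the objective. This is a mismatch between two printed sentences rather than a missing detail.

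**The non-infectious group may not belong in the denominator.** The endpoint is restricted to patients with LRTI and/or sepsis. General study design lists non-infectious disease as an alternative to these, and the sample-size section enrols that group for a different contrast. This stands, so the figures without that group come first and those with it are the alternative reading.

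**Stronger conclusions a reader might draw.** A reader might infer that an uninformative set would pass the 70% null value used in the sample-size section. The article uses that value for bacterial versus viral and for infected versus non-infected patients, and attaches no test or threshold to the Gram-subtype endpoint, so no pass probability can be claimed. A reader might also infer that such a set would look good for every subtype and in every age group. It would not: the paediatric figure is lower for a rare subtype, and in adults the specificity is low to moderate throughout.

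**Conclusion.** The concern holds as a stated mismatch between a secondary objective and its only endpoint. That conclusion rests on the text alone.

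The size is illustrative. It rests on the article's case mix and consensus rate, an assumed 90%/10% marker set, and an assumed Gram-positive share of 30% to 70%. Under these, a set with no subtype information shows about 75% to 83% specificity for Gram-positive disease in children (78% to 84% with the non-infectious group), against 10% for the comparator that the objective names. At a 10% share the paediatric figure is about 72% to 75%. In adults the range is about 40% to 57% (54% to 69%), so identical marker behaviour gives clearly different specificities through case mix alone. A set that separates bacterial from viral disease less well would show lower figures.

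The endpoint is secondary and carries no sample-size claim, so this does not threaten the primary result. It should still be corrected, because the endpoint as worded cannot support a conclusion about separating bacterial subtypes.

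**What to change.** Define the endpoint for this objective as the sensitivity and specificity of host biomarker sets for each bacterial subtype against the other bacterial subtypes, among patients with a bacterial reference diagnosis and an assigned subtype. Keep the comparison with all other aetiologies as a supplementary result. Say whether non-infectious patients count in it, and report it separately for children and adults because it depends on case mix.

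The cost is a change of wording and a restricted analysis set, with no new patients or data. The price is precision. At a 50% share the paediatric specificity denominator falls from 266 (342 with the non-infectious group) to 38. For an assumed specificity of 80%, the approximate 95% half-width goes from 1.96 × √(0.8 × 0.2 / 266) = 4.8 points to 1.96 × √(0.8 × 0.2 / 38) = 12.7 points. It would be wider still if some bacterial patients have no assigned subtype. The wider interval reflects the information actually available on the subtype question.

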### Sample size calculation

The following power analysis aims to achieve the primary study objective of developing a new diagnostic model for classifying patients with viral and bacterial aetiologist and treatment algorithms to guide antimicrobial prescribing.

#### Paediatric population analysis

First, we estimate the sample size required to reject the null hypothesis that the sensitivity over the entire population, P, is lower than P0 = 70% (H0: P ≤ P0, H1: P > P0) with significance level of 1% (α = 0.01), power of 80% (=1-β) for a true sensitivity P1 of 90% (P1 - P0 ≥ 0.2). For sufficiently large sample sizes (n > ~ 30) the sample distribution of the sensitivity, is approximately normally distributed, ($$ \widehat{p} $$ ~ N{P, P(1-P)/n}). Thus, the number of bacterial patients that are required is:$$ \mathrm{n}=\frac{{\left({\mathrm{Z}}_{1-\upalpha}\sqrt{{\mathrm{P}}_0\left(1-{\mathrm{P}}_0\right)}+{\mathrm{Z}}_{1-\upbeta}\sqrt{{\mathrm{P}}_1\left(1-{\mathrm{P}}_1\right)}\right)}^2}{{\left({\mathrm{P}}_1-{\mathrm{P}}_0\right)}^2}\le 76 $$

We estimate that the ratio between bacterial and viral paediatric patients is 1:3 and that expert consensus is achieved in 65% of the cases. Thus, the number of patients with an acute infection required in order to reach 76 bacterial patients is 468 = (76 / 25% / 65%). Using similar considerations for computing specificity the sample size for viral patients is also 76. Of note, we anticipate that the above mentioned 468 patients will include 229 (= 468 × 75% × 65%) viral patients, and thus there is no need for additional patients. To assess the host-response based diagnostics accuracy in differentiating patients with an acute infection (both viral and bacterial) and non-infectious patients, assuming P0 = 70% (H0: P ≤ P0, H1: P > P0) with significance level of 1% (α = 0.01), power of 80% (=1-β) for a true sensitivity P1 of 90% (P1 - P0 ≥ 0.2) requires 76 non-infectious patients. Overall, the paediatric cohort should include at least 468 patients with a suspected infectious disease and 76 patients with non-infectious.

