## Methods

### General study design

In this prospective, multi-centre, observational study, an expected total number of 1200 paediatric and adult patients aged 1 month and older with suspected LRTI and/or sepsis or a non-infectious disease are recruited, in order to develop a diagnostic model to differentiate between bacterial and viral infections. The study will generate a model for patients with LRTI and a separate model for patients with sepsis. The prediction of the model obtained from each patient will be compared with a consensus diagnosis by a panel of three experts in order to determine its accuracy (Fig. 2). The study is a non-interventional study, and therefore, the diagnostic prediction of the model will not be used for any clinical or diagnostics decision making. Local data monitor plans were used and executed by local, independent monitors.

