#### Adult population analysis

Using the same model as for the paediatric populations (assuming α = 0.01, 1-β = 0.2, P1 = 90%, P0 = 70% and a consensus rate of 65%) and assuming a viral to bacterial rate of 3:7 yields 390 patients with an infectious disease. Additionally, 76 non-infectious patients will be enrolled (based on similar calculations as for the paediatric population).

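### The printed sample size formula gives 44 patients per class, not the 76 used as the requirement, so the stated 80% power does not describe the design (it is about 98%)

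*Protocol article*

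**What the plan says.** All inputs appear in the protocol article under Paediatric population analysis. The hypotheses are directional, "H0: P ≤ P0, H1: P > P0", and the null sensitivity "is lower than P0 = 70" per cent. The error rates and the alternative are given as "significance level of 1% (α = 0.01), power of 80% (=1-β) for a true sensitivity P1 of 90" per cent. The formula printed there is the normal-approximation formula for one proportion against a fixed value, with Z at 1-α (one-sided). Its result is shown as ≤ 76.

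From then on 76 is the required number. For children with infection: "Thus, the number of patients with an acute infection required in order to reach 76 bacterial patients is 468", obtained by dividing 76 by a 25% bacterial share and a 65% consensus rate. The same 76 is given for viral patients and for non-infectious children.

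Adult population analysis says it applies the same model, "assuming α = 0.01, 1-β = 0.2, P1 = 90%, P0 = 70% and a consensus rate of 65" per cent. With a viral to bacterial rate of 3:7 it reaches 390 adults with infection, plus 76 non-infectious adults.

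**The concern.** Every input to the formula is printed beside it, so a reader can check the result, and it does not come out at 76. The section states no dropout allowance, safety margin or other inflation that would raise the formula's answer. The 65% consensus rate is applied afterwards, as a separate step.

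This calculation is the article's only quantitative basis for enrolment, and all four group targets depend on the one figure. If 76 is not what the formula gives, the stated 80% power is not the power of the design. The study takes research blood samples and nasal swabs from children and adults, so its size should rest on a calculation that can be reproduced.

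**Working it through.** **Inputs (Paediatric population analysis).** P0 = 0.70; P1 = 0.90; α = 0.01, one-sided (directional alternative, Z at 1-α), so Z = 2.3263; power 0.80, so Z = 0.8416.

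**Step 1: the printed formula.**

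n = (Z₁₋α √[P0(1-P0)] + Z₁₋β √[P1(1-P1)])² / (P1-P0)²

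= (2.3263 × √0.21 + 0.8416 × √0.09)² / 0.20²

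= (1.0661 + 0.2525)² / 0.04 = 43.46, so 44.

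The plan's figure of 76 is not reproduced. It is 76/44 = 1.73 times the formula's answer.

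**Step 2: do common variants give 76?** With α = 0.01 and 80% power kept:

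| Variant | One-sided | Two-sided |
|---|---|---|
| Printed formula | 44 | 52 |
| With continuity correction | 49 | 57 |
| Exact binomial, smallest n | 44 | 52 |
| Null variance in both terms | 53 | 62 |
| Alternative variance in both terms | 23 | 27 |
| Maximum variance (0.25) | 63 | 73 |
| Worst case over P0, difference fixed at 0.20 | 61 | 71 |

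None gives 76.

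**Step 3: the steps after 76.** These are right.

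- Children: 76 / 0.25 / 0.65 = 467.7, so 468.
- Adults: 76 / 0.30 / 0.65 = 389.7, so 390.

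The fault is confined to the 76 itself.

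**Step 4: power with 76 in a class, true value 90%.**

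- Normal approximation: Φ[(0.20 × √76 - 2.3263 × √0.21) / √0.09] = Φ(2.258) = 98.8%.
- Exact binomial: reject at 63 or more correct of 76; size 0.0076; power 98.2%.
- Put the other way, 76 patients give 80% power at a true value of about 85.7% (normal approximation).

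For comparison, with 44 patients the exact test rejects at 38 or more; its size is 0.00998 and its power 85.4%.

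**Step 5: the adult entry.** Read literally, 1-β = 0.2 makes Z₁₋β = -0.8416. The formula then gives (1.0661 - 0.2525)² / 0.04 = 16.5, so 17, which cannot lead to 390. The 390 follows only from the same 76 as in children.

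**The case against.** The best defence is the inequality sign. The article prints ≤ 76, and 43.46 is indeed below 76; the paediatric cohort is also set as a minimum. Read that way, 76 is an upper bound and nothing printed is false. This does not stand. The text goes on to use 76 as the number required for bacterial, viral and non-infectious patients alike, and gives no basis for a bound.

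The second defence does stand: the error is conservative. The stated 80% power is exceeded, so no test is weakened. That limits the severity.

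A reader might infer more than the documents support:

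- **That a two-sample formula was used by mistake.** The unpooled version gives (2.3263 + 0.8416)² × (0.21 + 0.09) / 0.04 = 75.27, so 76. But the pooled version gives 79, and the printed formula taken at its worst case over P0, two-sided and with continuity correction, gives 75.72, also 76. The article points to none of these, so the origin of 76 is unknown.
- **That enrolment should be cut to 44 per class.** Exact power is not stable there: 74.3% at 43, 85.4% at 44, just under 80% at 48, and above 80% from 49. The article also plans separate LRTI and sepsis models, two stages, and an inconclusive result category. Whether to use fewer patients is a trade-off that this arithmetic does not settle.
- **That adults have only 20% power.** The adult section says it uses the paediatric model, and 390 confirms it. The entry is a slip for β = 0.2.
- **That the total is contradictory.** The derived targets sum to 468 + 76 + 390 + 76 = 1010, while the study design section gives "an expected total number of 1200 paediatric and adult patients aged 1 month and older". An expected total above a minimum is no contradiction, and a condensed article may leave the reason for the margin to the full protocol.

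**Conclusion.** The point holds in a limited form. The printed formula with the stated inputs gives 44 per class. The 76 used instead is not derivable from them, and 468, 390 and both non-infectious groups of 76 carry it forward. The stated "power of 80% (=1-β) for a true sensitivity P1 of 90" per cent does not describe a design with 76 per class, whose power at that value is about 98%.

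The 98% assumes that 76 patients with a consensus diagnosis in the class all enter the test, each with a conclusive model result, and that α is 0.01 one-sided against 70%. It refers to the scarcer infection class in each age group (bacterial in children, viral in adults) and to the non-infectious groups. If inconclusive results were left out of the test, fewer than 76 would count and power would be lower.

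Severity is moderate: a sample size and a power on which the plan relies are wrong as written, but the error adds power and takes none away. The adult 1-β entry is editorial and changes no target.

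**What to change.** Keep 76 per class and the existing enrolment targets, and correct the text in one of two ways:

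1. State that the printed formula with the stated inputs gives a minimum of 44 per class, and that 76 consensus-diagnosed patients per class give about 98% power at a true 90% (98.2% exact binomial, 98.8% normal approximation). Replace the ≤ 76 by the formula's actual result.
2. If 76 came from other inputs or another method, state them in place of those printed, so that the figure can be reproduced.

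In Adult population analysis, change the entry to 1-β = 0.8.

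The cost is a few sentences in the sample size section. It needs no extra patients and no change to study conduct or enrolment targets.

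### The printed one-sample formula gives 44 patients per class, not 76, so the enrolment targets are larger than the stated 80% power requires

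*Protocol article*

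**What the plan says.** Under Sample size calculation, Paediatric population analysis, the article sets up a test of one proportion against a constant. The hypothesis to be rejected is that "the sensitivity over the entire population, P, is lower than P0 = 70" per cent, written as "H0: P ≤ P0, H1: P > P0", with a "significance level of 1% (α = 0.01") and a "power of 80% (=1-β) for a true sensitivity P1 of 90" per cent. The estimated sensitivity is given the single-sample variance P(1-P)/n, and the matching one-sample formula is printed with its result shown as ≤ 76.

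The text then uses 76 as the number needed. With one bacterial child to three viral and a 65% rate of expert consensus, "the number of patients with an acute infection required in order to reach 76 bacterial patients is 468". For specificity: "Using similar considerations for computing specificity the sample size for viral patients is also 76". The comparison of infected with non-infectious children is also given 76.

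The Adult population analysis applies the same model. It prints the power as 1-β = 0.2 and, "assuming a viral to bacterial rate of 3:7 yields 390 patients with an infectious disease", to which a further 76 non-infectious adults are added.

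**The concern.** A reader who puts the stated inputs into the printed formula does not get 76, or anything near it. Every target in the two sample size sections rests on that figure, so the stated power and the stated numbers do not belong together. At stake is whether the sample size for the primary endpoint can be reproduced, and whether 76 per class is a statistical minimum, as the text presents it. The direction of the error matters as much as its presence: too small a number would threaten the study, while too large a number means that the stated power and the described requirement are wrong.

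**Working it through.** **Inputs** (all from Paediatric population analysis unless noted)

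- One-sided α = 0.01, so z = 2.3263. The formula is printed with Z at 1-α.
- Power 80%, so z = 0.8416.
- P0 = 0.70: P0(1-P0) = 0.21, square root 0.45826.
- P1 = 0.90: P1(1-P1) = 0.09, square root 0.30.
- Squared difference: 0.2² = 0.04.
- Children: 25% bacterial, 65% consensus. Adults (Adult population analysis): 30% viral, 65% consensus.

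**1. The article's steps after 76 reproduce.**

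- 76 / 0.25 / 0.65 = 467.7, so 468.
- 76 / 0.30 / 0.65 = 389.7, so 390.
- Sum of the four components: 468 + 76 + 390 + 76 = 1010.

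The discrepancy therefore lies in the 76 itself.

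**2. The printed formula.**

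n = (2.3263 × 0.45826 + 0.8416 × 0.30)² / 0.04 = (1.06605 + 0.25248)² / 0.04 = 1.7385 / 0.04 = 43.46, so 44.

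**3. One-sample variants at the stated α and power.** None gives 76.

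| Variant | n |
|---|---|
| Two-sided α | 51.3, so 52 |
| Continuity correction, one-sided | 45.9, so 46 |
| Null variance only, one-sided | 52.7, so 53 |
| Maximum variance 0.25, one-sided | 62.7, so 63 |
| Maximum variance 0.25, two-sided | 73 |
| Largest over any P0 with a 0.2 difference, one-sided / two-sided | 60.7 / 70.8 |
| Exact binomial, one-sided | 44 (49 if power must stay at or above 80% for every larger n) |

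**4. A formula that does give 76.** The unpooled comparison of two independent groups, per group:

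(2.3263 + 0.8416)² × (0.21 + 0.09) / 0.04 = 10.036 × 0.30 / 0.04 = 75.27, so 76.

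The pooled version gives 79. The test described has no second group.

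**5. Power of the stated test.**

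- At n = 76, normal approximation: Φ((0.2 × √76 - 1.06605) / 0.30) = Φ(2.258) = 98.8%.
- At n = 76, exact binomial: reject at 63 or more of 76; α = 0.0076, power 98.2%.
- At n = 44, exact binomial: reject at 38 or more of 44; α = 0.00998, power 85.4%.
- With n = 76, 80% power is reached at a true value of about 85.6% against 70%.

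**6. Targets on the stated inputs.**

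- Children with infection: 44 / 0.25 / 0.65 = 270.8, so 271 (stated 468).
- Adults with infection: 44 / 0.30 / 0.65 = 225.6, so 226 (stated 390).
- Non-infectious: 44 per age group (stated 76).
- Sum: 271 + 44 + 226 + 44 = 585 (stated components 1010).

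**7. The adult power figure.** Taken literally, 1-β = 0.2 gives (1.06605 - 0.25248)² / 0.04 = 16.5, so 17 per class. The printed 390 follows from 76, not from 17, so this is probably a slip for β = 0.2.

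**8. What Stage B can hold.** Study stages reserves about 300 patients for validation. If all 300 were infected children, there would be 300 × 0.25 × 0.65 ≈ 49 bacterial consensus cases. If all were infected adults, there would be 300 × 0.30 × 0.65 ≈ 58 viral ones. A real mix with non-infectious patients would give fewer of each.

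**The case against.** The best defence has four parts.

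- **The printed inequality is true.** 43.46 is indeed ≤ 76. This does not rescue the derivation, because the text introduces the figure as the number required, divides it by 25% and 65%, and repeats it for the viral and non-infectious groups. Nothing calls it a chosen margin.
- **The error is on the safe side.** This stands. Type I error is not inflated, the promised power is exceeded, and the paediatric targets are worded as minima. A reader might infer that the enrolment targets are invalid or the study underpowered for this test. The documents do not support that: the targets are more than sufficient for the stated inputs. Nor do they show that the overall 1200 or the 900/300 split derives from 76, or that 76 serves as a stopping or subgroup rule.
- **The two-group origin is not documented.** This also stands. It is inferred from an exact numerical match.
- **Replacing 80% with 98% could mislead.** This stands too, and it shapes the fix. The 98% needs 76 evaluable patients of one class in a single independent test set, each given a definite result. The 468 and 390 are not assigned to either stage. Stage A data build the model, Stage B cannot supply 76 bacterial children or 76 viral adults, and the accuracy methods allow an inconclusive result for which the calculation makes no allowance.

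**Conclusion.** The sample size statement is wrong as written, in the conservative direction. The printed formula with the printed inputs gives 44 per class. The 76 used is about 1.7 times that (76/44 = 1.73), and it makes 468, 390 and the two non-infectious groups larger than 80% power requires. A single test on 76 patients has about 98% power at 90% versus 70%.

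This rests on reading the test as the article states it: one sample, one-sided, α = 0.01, and 80% power for adults as well as children. Two-sided α would give 52 and leave the conclusion unchanged.

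A reader might go further and conclude that the study could shrink to 585 patients. That does not follow. The calculation covers one test per class, while the same study must also develop the model and validate it in a separate cohort.

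This is a reporting error that should be corrected. It does not threaten the trial's validity.

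**What to change.** Leave enrolment as it is and revise the paediatric and adult sample size sections in one of two ways:

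- print the formula that actually produced 76 and justify it for a test against a fixed value; or
- state that the printed formula gives 44 (exact binomial: reject at 38 or more of 44, power 85%), and that 76, 468 and 390 are deliberately above that minimum.

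In either case, add a qualified statement of power, for example: *76 evaluable, conclusively classified patients per class in a single independent test set would give about 98% power at 90% versus 70%, or 80% power at a true value of about 86%; this is not the power of the Stage B validation cohort.*

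In the same edit, correct 1-β = 0.2 in the adult section so that it agrees with the 80% power in the paediatric section.

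The cost is rewording only: no additional patients, samples or procedures.
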